
### Biological specimen collections

During the clinical study, the blood, urine and feces will be collected from all participants with written informed consent on 2nd and 10th week, respectively. All samples will be delivered to the laboratory of the School of Chinese Medicine, Hong Kong Baptist University and be stored at − 80 °C for the metabolomics and metagenomics sequencing analysis. Blood, urine and fecal samples will be collected to analyze the metabolites profile of gut microbiota and the host before and after the treatment. Metagenomics sequencing will be used to monitor the gut microbiota composition profile before and after treatment. Both metabolomics and metagenomics sequencing are served as the methods to explore the mechanism of the Chinese medicine JCM-16021 attenuating the bowel symptoms by modulating gut microbiota.

### Sample size calculation

From our previous study, improvement rate on the GAI was 52% in the Chinese medicine JCM-16021 group and 32% in western medicine group, respectively [18]. According to the previous clinical trial guidelines for pharmacological treatment of IBS, a 15% improvement of the global outcome measure over placebo could be considered as a clinically significant therapeutic gain [31]. We assumed that there would be a 15% difference in the proportion of participants who report an improvement in their global symptoms after 8 weeks of treatment (either slight, moderate, or substantial) between the placebo group and the Chinese medicine JCM-16021 group. Thus, 166 participants are required in each group with 80% power and two-sided 5% alpha. Further assuming a 15% drop-out rate, a total of 392 participants (196 per arm) will be enrolled to ensure that the study is sufficiently powered to answer the research question of interest.

### Statistical analysis

Baseline data will be descriptively summarized. Categorical variables will be summarized by frequencies and percentages. Continuous variables will be summarized with mean and standard deviation [mean ± SD].

For the outcome analysis, comparisons between two groups for continuous variables will be conducted by using an analysis of variance (ANOVA), with other confounding factors like a multicenter character conducting the covariate analysis. Statistical analysis for the data which do not meet above conditions (e.g., non-normal) will be conducted with the use of non-parametric test. Categorical data of different groups will be reported as frequency (proportion). Comparisons between groups for these categorical data will be assessed with the use of chi-square test (CMH test) or non-parametric testing. For the repeatedly measured outcomes, the difference with the baseline data (follow-up minus the baseline) will be analyzed and the baseline data will be included in the model as covariables. Subgroup analyses will be carried out irrespective of whether there is a significant treatment effect on the primary outcome. The participants’ drop-out will be descriptively summarized. Both per-protocol analysis (PP) and intention-to-treat (ITT) analysis will be used to conduct the efficacy analysis. All treatment groups’ comparisons except for the primary outcome will be performed at a two-sided level of 0.05.

The safety analysis will mainly be performed by analysis of the incidence of adverse events between groups and the incidence of abnormal laboratory data before and after treatment between groups. A detailed description of the statistical analysis plan (SAP) is provided in Additional file 3.

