Participants will be excluded if they are constipation predominant, mixed or unsubtyped IBS, abnormal colonoscopy within 5 years (except for benign polypectomy or hemorrhoids), with severe diseases on the system of heart, lung, liver, and kidney which are diagnosed by TCM theory, concomitant diabetes, Glucose-6-Phosphate Dehydrogenase deficiency, unstable hypertension, malignant tumor or have undergone thyroid surgery or medication within a year, and with diseases on the Spleen-Stomach system or other diseases that affect the movement of Qi on the Spleen-Stomach system, which are diagnosed by TCM theory. Participants with current concomitant medication with effects on gastrointestinal function (e.g., anticholinergic drugs, calcium channel blockers, 5-HT3 receptor antagonists, antidiarrheal agents, antacids, prokinetic agents, antidepressants, anxiolytics and intestinal flora regulating drugs), medical history of gastrointestinal surgery (except for appendicitis surgery), serum levels of alanine transaminase (ALT), aspartate transaminase (AST), and creatinine (Cr) exceed 1.5 times of the reference limit, history of allergy in Chinese medicine, and medical history of neurological diseases or psychiatric disorders will also be excluded. Women in pregnancy or breast-feeding, or subjects currently participating in another clinical trial or taking IBS treatment drugs within 1 week are not eligible to be enrolled in this study.

During the study, participants may opt to withdraw at any time. Those who are lost to follow up or withdraw from the study after randomization will be treated as drop-out cases.

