### Safety outcome

In this study, adverse events (AEs) or SAEs related to IMPs are used for safety evaluation, including new incurrence symptoms or diseases, abnormal vital signs, clinically significant abnormal laboratory examination on renal or liver function. The severity of AEs is graded based on the Common Terminology Criteria for Adverse Events v4.0.

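### The main laboratory safety comparison counts abnormal results, although entry admits ALT, AST and creatinine up to 1.5 times the limit; a baseline-adjusted comparison would be a cheap, minor improvement

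*Protocol article*

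**What the plan says.** The safety paragraph of the Statistical analysis section reads: "The safety analysis will mainly be performed by analysis of the incidence of adverse events between groups", together with "the incidence of abnormal laboratory data before and after treatment between groups". It gives no cut-off for abnormal and does not say whether the counts are group totals at each time or changes within a person. It then refers onward: "A detailed description of the statistical analysis plan (SAP) is provided in Additional file 3". That file is not at hand.

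The Inclusion and exclusion criteria section, and the registration table (Table 1), exclude participants only when ALT, "aspartate transaminase (AST), and creatinine (Cr) exceed 1.5 times of the reference limit". Values between 1 and 1.5 times the limit are therefore admitted.

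The Safety outcome section counts as adverse events "clinically significant abnormal laboratory examination on renal or liver function", and adds: "The severity of AEs is graded based on the Common Terminology Criteria for Adverse Events v4.0".

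For repeatedly measured outcomes, the outcome-analysis paragraph of the Statistical analysis section plans an analysis of change in which "the baseline data will be included in the model as covariables". Nothing there says that this extends to laboratory values.

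**The concern.** Two things do not fit well together.

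- **A ceiling for some participants.** If abnormal means above the reference limit, anyone who enters at 1 to 1.5 times the limit is already in the abnormal category. Further worsening in that person leaves the count unchanged.
- **Loss of information for everyone else.** Each analyte is a continuous measurement with its own pre-treatment value. An incidence keeps only which side of a cut-off it falls on. A moderate rise across the arm that carries few people over the limit leaves little trace.

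Safety is one of the two objectives, and liver and renal function are the laboratory concerns that the article names. A laboratory comparison does not depend on an investigator calling a result clinically significant, so it is the natural place to see an arm-wide shift. If it is insensitive, a null result may be read as more reassuring than it is.

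**Working it through.** **1. The plan's own figure, for the number per arm.** The article gives no sample size or power for laboratory data, so the available number comes from the primary outcome. I take 32% as the control rate (the article quotes it for western medicine; using it for placebo is my assumption), and 47% for the active arm. With p̄ = 0.395:

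n = [1.96·√(2·0.395·0.605) + 0.8416·√(0.32·0.68 + 0.47·0.53)]² / 0.15² = (1.355 + 0.575)² / 0.0225 = 165.5, so 166.

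166 / 0.85 = 195.3, so 196 per arm and 392 in total. The stated figures reproduce. I use 166 to 196 per arm below.

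**2. How many participants meet the ceiling.** Assumptions, since the article gives no laboratory data: log values normal with SD 0.45; 5%, 8% or 12% of the screened population above the limit; abnormal means above the limit. In SD units the limit is c = z(1−p), and the entry cut-off is t = c + ln(1.5)/0.45 = c + 0.901. The share entering between them is [Φ(t) − Φ(c)] / Φ(t). For 8%: c = 1.405, t = 2.306, share = (0.9894 − 0.9200)/0.9894 = 7.0%.

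| Above limit at screening | Entering at 1-1.5 times | Of 166 per arm |
|---|---|---|
| 5% | 4.5% | about 7 |
| 8% | 7.0% | about 12 |
| 12% | 10.3% | about 17 |

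The ceiling affects a small minority. Most of the loss below comes from dichotomising.

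**3. Cost of dichotomising, closed form.** Take a uniform shift of 0.3 SD, 166 per arm, two-sided 5%.

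- Values, unadjusted: 0.3·√(166/2) − 1.96 = 2.733 − 1.96 = 0.773; Φ = 78%.
- Values, baseline correlation 0.5: 2.733/√(1 − 0.25) − 1.96 = 1.196; Φ = 88%.
- Incidence, 5% above the limit in controls: active rate = 1 − Φ(1.645 − 0.3) = 8.9%; power for 5% against 8.9% is 29%.
- Incidence, 10% in controls: active rate 16.3%; power 40%.

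With 196 per arm the four figures are 84%, 93%, 33% and 46%.

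**4. The same with the entry cut-off, by simulation.** Baseline values are truncated at 1.5 times the limit, follow-up = r·baseline + noise + shift, r = 0.5 to 0.7, 166 per arm. Post-treatment abnormal proportions are compared by an uncorrected two-sample test, and values by ANCOVA.

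| Uniform shift | Change in value | Power, incidence | Power, baseline-adjusted |
|---|---|---|---|
| 0.25 SD | exp(0.25·0.45) = 1.12 | about 20-33% | 73-90% |
| 0.35 SD | exp(0.35·0.45) = 1.17 | 37-58% | 95-100% |

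In one middle setting (8% above the limit, r = 0.7, 0.25 SD), abnormal rates are 7.3% against 11.7%, with power 29% against 90%.

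**5. A different kind of effect.** Keep the assumptions of step 4, but give 8% of the active arm a fourfold rise and the rest no change. Power is 42-68% for incidence, 52-76% for the proportion whose grade rises, and 56-70% for baseline-adjusted values. With 5% above the limit and r = 0.5, incidence is ahead of the adjusted comparison, 64% against 57%.

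**The case against.** A reader might infer that laboratory values are compared only as normal or abnormal, and that worsening in participants who enter above the limit cannot register anywhere in the safety assessment. The documents support neither. The safety paragraph says that the analysis is done mainly this way and refers to an analysis plan that is not shown. Shift tables, change from baseline and a definition of abnormal are ordinary content for such a plan.

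The ceiling also rests on one reading of abnormal. The only numerical laboratory threshold in the article is 1.5 times the limit, and elsewhere the article speaks of clinically significant abnormality. On either of those readings, a value of 1.4 times the limit need not count as abnormal at entry. Even on the ordinary reading, a rise from 1.4 to 4 times the limit would probably be recorded as a clinically significant, CTCAE-graded adverse event and so enter the between-group comparison of adverse events.

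It is also tempting to say that a real upward shift would usually be reported as no difference. That depends on the kind of effect: step 5 shows the advantage of adjusted values shrinking or reversing. Low power for safety contrasts is normal in a trial sized on efficacy, and randomisation balances participants who are abnormal at entry in expectation, so the incidence comparison is valid.

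All of this stands, and it reduces the point to a minor one. What it does not remove is that incidence is the stated principal laboratory analysis, and that the adverse-event route works person by person through investigator judgement. An arm-wide moderate shift can pass both.

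**Conclusion.** The point holds in a limited form. The article's named laboratory comparison fits poorly with an entry rule that admits values up to 1.5 times the limit, if abnormal means above the reference limit. It is also a weak detector of a moderate uniform shift: about 20-33% power at 0.25 SD, where the same values adjusted for baseline give 73-90%. Those figures rest wholly on assumed distributions, abnormal rates and correlations; only the number per arm comes from the article. For a few large rises the difference is small or absent. This is a minor, inexpensive improvement to a stated method. No stated figure is wrong.

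**What to change.** In the safety paragraph of the Statistical analysis section, define abnormal, keep the abnormal counts before and after treatment as description, and add for each of ALT, AST and creatinine:

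- (a) the post-treatment value on the log scale, compared between arms with the pre-treatment log value as covariate and reported as a ratio with 95% confidence interval;
- (b) a cross-tabulation of pre- by post-treatment CTCAE v4.0 grade, comparing between arms the proportion whose grade rose.

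The two complement each other: (a) is sensitive to a shift across the arm, and (b) shows individual worsening relative to the participant's own starting grade. If the unseen analysis plan already contains them, the article need only say so.

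The cost is wording plus one model and one table per analyte. No new samples, visits or participants are needed; the article already refers to laboratory data before and after treatment, and follow-up is complete. The change should be settled before the blinding code is broken. The downside is that small shifts of doubtful clinical importance may be reported; the ratio with its interval and the grade table put them in context.

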## Discussion

Irritable Bowel Syndrome (IBS) is a persistent or intermittent episode of functional gastrointestinal disease with abdominal pain, bowel habits and/or stool traits that change clinically [32]. Many people with IBS are eager for an effective treatment. However, at present, due to the complexity and uncertainty of its etiology, there is no clear biochemical diagnostic index and current treatment is not very satisfactory. Therefore, it is important to investigate an effective medicine for IBS. Many RCTs have suggested that TCM formulas have significant efficacy for IBS symptoms. The mechanisms of these TCM formulas are likely related to the regulation of neurotransmitters and hormones in the enteric nervous system, attenuation of intestinal inflammation and restoration of intestinal flora, etc. [33, 34]. JCM-16021 is a new Chinese medicine formula developed by our team for the treatment of IBS-D based on the Chinese medicine theories and clinical experience. Our research group has conducted a series of studies on the Chinese medicine JCM-16021 to evaluate its pharmacology, efficacy, safety for more than 10 years. In the previous small scale clinical trial, it has shown a trend that participants with the Chinese medicine JCM-16021 had the greatest extent of improvement at the end of 8-week treatment and the end of 8-week follow up [16]. But a large scale trial is needed to further evaluate the efficacy and safety of this formula for IBS-D. Recently, disorder of the gut microbiota has been considered to be one of potential aetiological factor [32, 35–37]. Our previous basic studies have also shown that the Chinese medicine JCM-16021 could effectively relieve intestinal hyperalgesia by altering the gut microbiota and improving the co-metabolism of the gut microbiota and its host, and also through regulating host’s immune response to gut microbiota as well as enhancing gut barrier. It is likely to be an important mechanism for the effective treatment of IBS-D with the Chinese medicine JCM-16021[38]. This study will provide an opportunity to reassess the mechanism in a large scale trial.

## Conclusion

In conclusion, this protocol will provide details for investigators about the study following SPIRIT Statement for Chinese Herbal Medicine Formulas. This study has a larger sample size than our previous pilot study. It is believed that more higher-quality evidence on the efficacy and safety of the Chinese medicine JCM-16021 for IBS-D will be provided through strictly compliance with the protocol. The results may also help to discover the underlying mechanism of this herbal remedy for the condition.

## Trial status

Participants’ recruitment started in October 2018. Today, 392 participants have been recruited. The actual date for the start of recruitment was the 8th November 2018. The actual date for the end of recruitment was the 29th October 2020. The last participant completed the follow-up on 17th February 2021.

## Data Availability

The datasets will be available from the corresponding author on reasonable request.

## Abbreviations

IBS: Irritable bowel syndrome
TCM: Traditional Chinese medicine
IBS-SSS: Irritable bowel syndrome-symptom severity score
RCTs: Randomized clinical trials
LSSD: Liver stagnation and spleen deficiency
NMS: Neonatal maternal separation
EC: Enterochromaffin
5-HT: Serotonin
T_h_1-: T-cell type 1-
SPIRIT-TCM Extension 2018: Standard protocol items for clinical trials with traditional Chinese medicine 2018
CONSORT-CHM Formulas 2017: CONSORT extension for Chinese herbal medicine formulas 2017
SAEs: Serious adverse events
CRF: Case report form
ALT: Alanine transaminase
AST: Aspartate transaminase
Cr: Creatinine
IMP: Investigational medicinal product
GMP: Good manufactory practice
GAI: Global assessment of improvement
IBS-QoL: Irritable bowel syndrome-quality of life
AEs: Adverse events
GCP: Good Clinical Practice
CMH: Cochran-Mantel–Haenszel
ANCOVA: Analysis of covariance
PP: Per-protocol analysis
ITT: Intention-to treat analysis
REDCap: Research electronic data capture
SAP: Statistical analysis plan
